## 2. Detailed study description

### Background

Asthma is a heterogeneous, inflammatory airway disorder with complex pathophysiological mechanisms (1). Although in most asthma patients the disease can be well controlled with inhaled anti-inflammatory and bronchodilator medications, this treatment fails in about 5-10% of patients (2). These patients develop severe asthma, which is a debilitating disease, associated with frequent severe exacerbations, emergency visits, and hospitalizations, resulting in a poor quality of life. For many years patients with this condition were dependent on the chronic use of high-dose inhaled and oral glucocorticoids, which put them at increased risk for serious and often life-threatening adverse events (3). However, recently, new biologics for severe asthma have become available (4). These biologics target key cytokines of so called "Type 2" airway inflammation, interleukin(IL)-4, IL-5 and IL-13. Mepolizumab and Reslizumab bind to interleukin (IL)-5, Benralizumab binds to the IL-5 receptor, while Dupilumab binds to the alpha subunit of the IL-4 receptor, thereby blocking IL4 and IL13 signalling. Treatments with these biologics have already resulted in remarkable improvements of asthma symptoms and quality of life, although, for reasons that are not understood, not everyone benefits despite meeting the approved inclusion criteria (4). However, many questions about the natural history, burden and costs of severe asthma, disease mechanisms, identification of different phenotypes, prediction of therapy response remain unanswered (5). These questions will be answered in studies organized by the ERS SHARP CRC, using data from SHARP CENTRAL Registry as well as other, already established, registries of patients with severe asthma in Europe.

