- ☐ Negative (BHR not demonstrated, FEV1 decline  $< 20\%$ )

Has blood cell differential counting been performed in the last 5 years?

- ☐ Yes
- ☐ No

If yes, please report date of most recent result:

- Leukocytes: \_\_\_\_ x 10E9 and \_\_\_\_ %
- Neutrophils: \_\_\_\_ x 10E9 and \_\_\_\_ %
- Eosinophils: \_\_\_\_ x 10E9 and \_\_\_\_ %

If yes, what was the highest eosinophil count ever measured?

Has blood glucose or HbA1c been measured during the last year?

- ☐ Yes
- ☐ No

If yes, please report date of most recent result:

Fasting glucose level:

Hba1c level

Has Blood Gas Analysis been performed/

- ☐ Yes
- ☐ No

If yes, please report date of most recent result:

pH \_\_\_\_\_ pCO2: \_\_\_\_\_ kPa / \_\_\_\_\_ mmHg; pO2: \_\_\_\_\_ kPa /  
\_\_\_\_\_ mmHg;

Has total serum IgE testing been performed?

- ☐ Yes
- ☐ No

If yes, please report date of most recent result:

\_\_\_\_\_ IU/ml or kU/l

Has a routine allergy test RAST/CAP or skin prick testing even been performed?

- ☐ Yes, positive
- ☐ Yes, negative
- ☐ No

If yes, please report date of most recent result:

Has allergy to aspergillus ever been tested?

- ☐ Yes, positive
- ☐ Yes, negative
- ☐ No

If yes, please report date of most recent result:

Has allergy to food ever been tested?

- ☐ Yes, positive
- ☐ Yes, negative
- ☐ No

If yes, please report date of most recent result:

Has sputum analysis (cell counts) ever been performed?

- ☐ Yes
- ☐ Yes, but inadequate sample
- ☐ No

If yes, please report date of most recent result:

\_\_\_\_\_ % Eosinophils  
\_\_\_\_\_ % Neutrophils

Has sputum culture been performed during last year?

- ☐ Yes, positive for pathogens
- ☐ Yes, negative for pathogens
- ☐ Yes, throat bacteria
- ☐ No

If yes, please report date of most recent result:

Has Chest X-Ray ever been performed?

- ☐ Yes, findings compatible with asthma[LSEP]
- ☐ Yes, findings compatible with other pulmonary disorders
- ☐ Yes, normal findings
- ☐ No

If yes, please report date of most recent result:

Has Chest HRCT ever been performed

- ☐ Yes

☐ No

If yes, please report date of most recent result:

- ☐ Bronchiectasis[L]  
[SEP]
- ☐ Emphysema
- ☐ Tree-in-bud configurations
- ☐ Other pulmonary abnormalities
- ☐ No abnormal findings

Has DEXA-scan ever been performed

- ☐ Yes, pathological findings
- ☐ Yes, normal findings
- ☐ No

If yes, please report date of most recent result:

Has bronchoscopy ever been performed

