- ☐ Yes, findings compatible with asthma[L]  
[SEP]
- ☐ Yes, findings compatible with other lung diseases
- ☐ Yes, normal findings
- ☐ No

If yes, please report date of most recent result:

Does the patient have one of the following co-morbidities

Atopic dermatitis

- ☐ Yes
- ☐ No or very unlikely[L]  
[SEP]
- ☐ Only in the past
- ☐ Unknown

Allergic rhinoconjunctivitis

- ☐ Yes
- ☐ No or very unlikely[L]  
[SEP]
- ☐ Only in the past
- ☐ Unknown

[L]  
[SEP]

Chronic rhinosinusitis

- ☐ Yes
- ☐ No or very unlikely[L][SEP]
- ☐ Only in the past
- ☐ Unknown

[L][SEP]

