#### Gastroesophageal reflux

- ☐ Yes
- ☐ No or very unlikely[L][SEP]
- ☐ Only in the past
- ☐ Unknown

Frequent (>2/yr) respiratory infections requiring antibiotics?

- ☐ Yes
- ☐ No or very unlikely[SEP]
- ☐ Only in the past
- ☐ Unknown

Bronchiectasis

- ☐ Yes
- ☐ No or very unlikely[SEP]
- ☐ Unknown

EGPA (Churg-Strauß-Syndrome)

- ☐ Yes
- ☐ No or very unlikely[SEP]
- ☐ Unknown

Eosinophilic pneumonia

- ☐ Yes
- ☐ No or very unlikely[SEP]
- ☐ Only in the past
- ☐ Unknown

ABPA (Allergic bronchopulmonary aspergillosis)

- ☐ Yes
- ☐ No or very unlikely[SEP]
- ☐ Unknown

Chronic heart failure

- ☐ Yes
- ☐ No or very unlikely[SEP]
- ☐ Only in the past
- ☐ Unknown

OSA (Obstructive sleep Apnea)

- ☐ Yes
- ☐ No or very unlikely[SEP]
- ☐ Only in the past
- ☐ Unknown

Other co-morbidities

-----  
-----

Has adherence to therapy ever been checked?

- ☐ Yes  
☐ No[L]SEP

If yes, please report date of most recent result:

% ICS taken (per period checked): \_\_\_\_\_%

Has Inhalation technique been checked?

- ☐ Yes  
☐ No[L]SEP

If yes, date last instruction:

Does the patients currently take one or more of the following medications

If yes, which one and at what dose?

- ☐ SABA
- salbutamol  $\leq$  8 puffs/day
  - salbutamol  $>$  8 puffs/day
  - terbutaline  $\leq$  8 puffs/day
  - terbutaline  $>$  8 puffs/day
- ☐ Anticholinergics
- ipratropium
- ☐ Fixed SABA/anticholinergic combinations
- ipratropium / fenoterol  $\leq$  8 puffs/day
  - ipratropium / fenoterol  $>$  8 puffs/day
  - ipratropium / salbutamol  $\leq$  8 puffs/day
  - ipratropium / salbutamol  $>$  8 puffs/day
- ☐ LABA single inhaler
- formoterol[L]SEP \_\_\_\_\_ ug/day
  - salmeterol[L]SEP \_\_\_\_\_ ug/day
  - indacaterol \_\_\_\_\_ ug/day
  - olodaterol \_\_\_\_\_ ug/day

- ☐ ICS single inhaler
  - beclomethasone \_\_\_\_\_ug/day
  - budesonide[SEP]\_\_\_\_\_ug/day
  - fluticasone[SEP]\_\_\_\_\_ug/day
  - ciclesonide \_\_\_\_\_ug/day
- ☐ LAMA single inhaler:
  - tiotropium: \_\_\_\_\_ µg/day[SEP]
  - glycopyrronium:\_\_\_\_\_ µg/day
  - aclidinium: \_\_\_\_\_ µg/Day
- ☐ Fixed ICS/LABA combination inhaler
  - budesonide / formoterol
    - budesonide \_\_\_\_\_ µg/day and fFormoterol\_\_\_\_\_ µg/day
  - salmeterol / fluticasone

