    - salmeterol \_\_\_\_\_ µg/day and Fluticasone propionate\_\_\_\_\_ µg/day
  - beclomethasone / formoterol
    - beclomethasone \_\_\_\_\_ µg/day and formoterol \_\_\_\_\_ µg/day
  - fluticasone / formoterol
    - fluticasone \_\_\_\_\_ µg/day and formoterol \_\_\_\_\_ µg/day
  - fluticasone furoate/ vilanterol[SEP]
    - fluticasone fuorate \_\_\_\_\_ µg/day and vilanterol \_\_\_\_\_ µg/day
- ☐ Fixed LABA/LAMA combination inhaler
  - indacaterol / glycopyrronium
    - indacaterol \_\_\_\_\_ µg/day and glycopyrronium\_\_\_\_\_ µg/day
- ☐ montelukast
- ☐ theophylline
- ☐ Maintenance oral corticosteroids
  - predniso(lo)ne[SEP]\_\_\_\_\_ mg/day
  - dexamethasone \_\_\_\_\_ mg/day
  - betamethasone \_\_\_\_\_ mg/Day
  - hydrocortisone \_\_\_\_\_ mg/Day
  - triamcinolone (injections) \_\_\_\_\_ mg/month

Is patient currently tapering his/her oral/systemic corticosteroid dose?

- ☐ Yes
- ☐ No

Is the patient currently being treated with biologic therapy?

- ☐ Yes, omalizumab

Start date: dd/mm/yyyy

Dose per injection visit\_\_\_\_\_ mg

Frequency of dosing\_\_\_\_\_ weeks

Has omalizumab dose or interval been changed in last 12 months:

- ☐ Yes, because of adverse effects
- ☐ Yes, because of insufficient response
- ☐ Yes, because of (very) good response
- ☐ No

- ☐ Yes, mepolizumab

Start date: dd/mm/yyyy

Dose per injection/visit\_\_\_\_\_ mg

Frequency of dosing\_\_\_\_\_ weeks

Has mepolizumab dose or interval been changed in last 12 months:

- ☐ Yes, because of adverse effects
- ☐ Yes, because of insufficient response
- ☐ Yes, because of (very) good response
- ☐ No

- ☐ Yes, reslizumab

Start date: dd/mm/yyyy

Dose per infusion/visit\_\_\_\_\_ mg

Frequency of dosing\_\_\_\_\_ weeks

Has reslizumab dose or interval been changed in last 12 months:

- ☐ Yes, because of adverse effects
- ☐ Yes, because of insufficient response
- ☐ Yes, because of (very) good response

☐ Yes, dupilumab

Start date: dd/mm/yyyy

Dose per injection/visit\_\_\_\_\_ mg

Frequency of dosing\_\_\_\_\_ weeks

Has dupilumab dose or interval been changed in last 12 months:

- ☐ Yes, because of adverse effects
- ☐ Yes, because of insufficient response
- ☐ Yes, because of (very) good response
- ☐ No

☐ Yes, benralizumab

Start date: dd/mm/yyyy

Dose per injection/visit\_\_\_\_\_ mg

Frequency of dosing\_\_\_\_\_ weeks

Has benralizumab dose or interval been changed in last 12 months:

- ☐ Yes, because of adverse effects
- ☐ Yes, because of insufficient response

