- ☐ Yes, because of (very) good response

☐ No, patient is currently not treated with biologics

Does the patient currently use any of the following (non-pulmonary) medications?

- ☐ Nasal corticosteroids[L][SEP]
- ☐ Antihistamines[L][SEP]
- ☐ Bisphosphonates[L][SEP]
- ☐ Calcium suppletion ( $\pm$  vit D)[L][SEP]
- ☐ Proton pump inhibitors[L][SEP]
- ☐ vit K antagonists[L][SEP]
- ☐ NSAIDs[L][SEP]
- ☐ Other

-----  
-----  
-----

[L][SEP]

Has the patient received one of the following asthma add-on treatments  
IN THE PAST?

☐ omalizumab

If Yes, date of last administration (dd/mm/yyyy)

If yes, reason for stopping?

☐ insufficient reduction of systemic steroid dose[L]SEP

☐ Adverse effects[L]SEP

☐ Insufficient improvement of symptoms or exacerbations[L]SEP

☐ Insufficient improvement of lung function

☐ mepolizumab

If Yes, date of last administration (dd/mm/yyyy)

If yes, reason for stopping?

☐ insufficient reduction of systemic steroid dose[L]SEP

☐ Adverse effects[L]SEP

☐ Insufficient improvement of symptoms or exacerbations[L]SEP

☐ Insufficient improvement of lung function

[L]SEP

☐ reslizumab

If Yes, date of last administration (dd/mm/yyyy)

If yes, reason for stopping?

☐ insufficient reduction of systemic steroid dose[L]SEP

☐ Adverse effects[L]SEP

☐ Insufficient improvement of symptoms or exacerbations[L]SEP

☐ Insufficient improvement of lung function

[L]SEP

☐ benralizumab

If Yes, date of last administration (dd/mm/yyyy)

If yes, reason for stopping?

☐ insufficient reduction of systemic steroid dose[L]SEP

☐ Adverse effects[L]SEP

☐ Insufficient improvement of symptoms or exacerbations[L]SEP

☐ Insufficient improvement of lung function

[L]SEP

☐ dupilumab

If Yes, date of last administration (dd/mm/yyyy)

If yes, reason for stopping?

☐ insufficient reduction of systemic steroid dose[L]SEP

☐ Adverse effects[L]SEP

☐ Insufficient improvement of symptoms or exacerbations[L]SEP

- ☐ Insufficient improvement of lung function

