- ☐ methotrexate[L][SEP]
- ☐ cyclosporine[L][SEP]
- ☐ azathioprine[L][SEP]
- ☐ cyclophosphamide
- ☐ interferon alpha
- ☐ aspirin desensitization
- ☐ macrolide therapy (>6 weeks)
- ☐ immunotherapy
- ☐ other: \_\_\_\_\_

Which steroid-induced adverse effects were ever objectively diagnosed?

- ☐ Skin bruising / thinning[L][SEP]
- ☐ Weight gain[L][SEP]
- ☐ Cataract
- ☐ Hypertension[L][SEP]
- ☐ Osteoporosis[L][SEP]
- ☐ Diabetes mellitus[L][SEP]
- ☐ Depression[L][SEP]
- ☐ Other: \_\_\_\_\_
- ☐ Other: \_\_\_\_\_
- ☐ Other: \_\_\_\_\_
- ☐ Other: \_\_\_\_\_

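### Hypertension, diabetes, osteoporosis and cataract have a coded diagnosis box only under a steroid-induced heading, so the form cannot separate occurrence from site attribution

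*Protocol*

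**What the plan says.** The last question of Appendix 1 asks "Which steroid-induced adverse effects were ever objectively diagnosed" and offers tick-boxes for skin bruising or thinning, weight gain, cataract, hypertension, osteoporosis, diabetes mellitus and depression, plus free-text lines. It has no answer for none or unknown, no date, and no criterion for calling a condition steroid-induced.

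The separate block that opens with "Does the patient have one of the following co-morbidities" makes no reference to cause. Most of its items offer four answers (yes, no or very unlikely, past only, unknown). Depression is among them. Hypertension, diabetes, osteoporosis and cataract are not. The block ends with a free-text line, "Other co-morbidities".

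Elsewhere the form asks "Has DEXA-scan ever been performed" (pathological, normal or not done) and "Has blood glucose or HbA1c been measured during the last year" (with the values), and it lists "Bisphosphonates" among current non-pulmonary medications. Systemic steroid exposure is recorded as current use and dose under "Maintenance oral corticosteroids".

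The Background section says that chronic steroid use put patients at "increased risk for serious and often life-threatening adverse events". The objectives include phenotype, burden and, in general terms, predictors of adverse events. The Registry Data Points section names co-morbidities as a data item. The Statistical Analysis Plan section leaves analyses to each project.

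**The concern.** The steroid question merges two facts: whether the patient has the condition, and whether the site believes steroids caused it. The requirement of an objective diagnosis bears on the disease, not on the cause, so attribution is left to each site. A patient whose diabetes came before any systemic steroid, or whose hypertension the site considers unrelated, has no coded place for that diagnosis.

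Two uses of the data are affected. The first is plain description: these are ordinary co-morbidities of adults with severe asthma, and their coded frequency would be too low. The second is any later project that relates these boxes to steroid exposure. Sites may attribute more readily in patients who take oral steroids, and the difference in ticking would then be read as a difference in disease. A project's own analysis plan cannot recover a neutral diagnosis that the form did not collect.

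**Working it through.** The protocol states no figure for this item, so there is nothing to reproduce. The check is an inventory of fields, followed by a misclassification identity with assumed inputs.

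**1. Where each condition can be recorded in Appendix 1**

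| Condition | Coded co-morbidity item | Steroid-induced tick | Other coded or numeric field |
|---|---|---|---|
| Hypertension | no | yes | none |
| Cataract | no | yes | none |
| Osteoporosis | no | yes | DEXA result; current bisphosphonate use |
| Diabetes mellitus | no | yes | fasting glucose and HbA1c, if measured in the last year |
| Depression | yes, four answers | yes | not needed |

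All of them can also be written as free text. The Enrolment section mentions vital signs at yearly visits, but the form has height, weight and BMI and no blood-pressure field. No antihypertensive or antidiabetic drug is listed by name among the medications.

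**2. What an unticked box means.** It covers three states: condition absent, condition present but not attributed, and not assessed. The form does not distinguish them.

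**3. Effect on prevalence.** Let P be the true prevalence and a the share of true cases that the site attributes to steroids, with no tick in patients who lack the condition. Recorded prevalence is P × a. With assumed P = 30%, a = 0.4 gives 12% and a = 0.05 gives 1.5%. Only a = 1 recovers the true value.

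**4. Effect on a comparison.** Let subscript 1 denote steroid users and 0 comparators:

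apparent ratio = (P1 × a1) / (P0 × a0) = true ratio × (a1 / a0)

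None of these inputs is in the protocol. For illustration:

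- True ratio 1, a1 = 0.5, a0 = 0.2: 0.5 / 0.2 = 2.5.
- True ratio 1, a1 = 0.9, a0 = 0.1: 0.9 / 0.1 = 9.
- P1 = 40%, P0 = 30% (true ratio 1.33), a1 = 0.8, a0 = 0.4: 0.32 / 0.12 = 2.67.
- The same prevalences, a1 = 1.0, a0 = 0.05: 0.40 / 0.015 = 26.7.
- a1 = a0: the ratio is unbiased, but both prevalences are still understated unless the share is 1.

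The multiplier is simply a1 / a0. The examples show that the tick-list alone can create or inflate an association. They do not estimate how far it would.

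**5. Who the comparators would be.** The detailed inclusion criteria require medium or high doses of inhaled corticosteroids, and the form records only current systemic use. Comparators would be patients not on maintenance oral steroids at the visit. Some may have had earlier courses, and the question asks about effects at any time. A tick in this group is therefore possible, so a0 need not be near 0.

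**The case against.** The strongest objection is that the protocol plans no comparison of these conditions between steroid users and non-users. Analyses are left to later projects, and the Adverse Event Reporting section says that systematic documentation of treatment adverse events is not the registry's primary purpose. This stands, and it limits the severity. It does not remove the point, because the four conditions are also ordinary co-morbidities and their prevalence is affected without any comparison.

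A reader might infer that the outcome is defined by the exposure, so that any such comparison is circular and non-users would show almost no cases by construction. The documents do not support that. Every eligible patient uses inhaled steroids, earlier oral courses are possible, and the heading is not restricted to systemic or current use. The accurate description is differential misclassification that depends on attribution. A contrast before and after a biologic is a different matter, since the heading concerns steroids and the obstacle there is an undated item covering any time in the past.

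Neutral sources do exist, and this stands in part. DEXA and bisphosphonates inform on osteoporosis, and glucose and HbA1c on diabetes. They are incomplete. DEXA covers only scanned patients, and a pathological scan is not a recorded diagnosis. Bisphosphonate use is current only. Glucose and HbA1c are limited to the last year and can be normal under treatment. Free text serves all four conditions but is neither prompted nor coded, whereas the Data Quality section prefers coded answers where possible. Hypertension and cataract have nothing else.

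It might also seem that depression, asked in both places, is a contradictory duplicate. It is not: a neutral yes with the steroid box unticked is a coherent answer, and it is the structure that the other four conditions lack.

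**Conclusion.** The defect holds as a limitation of the form. Four conditions have a coded diagnosis only through a causal judgement, and an unticked box is ambiguous. Coded prevalence from this item is understated to the extent that sites do not attribute. Any later contrast by steroid exposure is biased by the factor a1 / a0 and is unbiased only if the shares are equal. The size cannot be fixed from the protocol. The range of 2.5 to 9 for a true ratio of 1 rests wholly on the assumed shares, and its direction rests on the assumption that sites attribute more often in users. The problem is greatest for hypertension and cataract and smaller for osteoporosis and diabetes. Because no stated endpoint or planned comparison depends on the item, this is a minor to moderate, inexpensive improvement, not a change that must precede further data collection.

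**What to change.** Add hypertension, diabetes mellitus, osteoporosis and cataract to the co-morbidity block, with the four-answer format already used for depression and a year of diagnosis. Keep the present steroid list as a separate item, relabelled as considered steroid-related by the site. Keep depression in both places, neutral in one and attributed in the other. Retain the weight-gain tick, because yearly weights cannot show gain before enrolment. State that the neutral items are the source for prevalence and for any comparison by steroid exposure, and that the attribution item describes site opinion.

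The cost is four answer groups with a year field, one relabelled question and a slightly longer form. Existing entries stay valid as site-attributed. The case-manager part is completed yearly, so patients still attending can supply the neutral answers at their next visit; patients who have left cannot. If the sponsor judges that the change falls under the Modification of the protocol section, an amendment with country-level ethics approval is a further cost, and the change could be bundled with the next planned amendment.
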